### EEG recording and processing

A total of 20 min of EEG signals will be recorded for each stimulation procedure, and 10 min will be acquired before and after taVNS. EEG will be acquired by 32 channels (Nicolet EEG V32, Natus Neurology, USA) at a sampling rate of 1000 Hz, and the device will have 32 Ag/AgCl electrodes based on the national standard 10–20 system setup. All electrodes will be used with FCz as the reference electrode and AFz as the ground electrode, and the skin/electrode impedance will be kept below 5 kΩ. Patients will be awake during the acquisition, and if they show signs of sleepiness, the CRS-R scale will be used to wake up the procedure, or the experiment will be paused. Thirty-two electrodes (Fp1, Fp2, F3, Fz, F4, F7, F8, FC1, FC2, FC5, FC6, C3, Cz, C4, CP1, CP2, CP5, CP6, Pz, P3, P4, PO3, PO4, PO7, PO8, O1, Oz, O2, T3, T4, T5, and T6) will be selected for offline EEG analysis, and the EEG display parameters will be set to trap 50 Hz and bandpass filtered to 1–40 Hz. The frontal, central, parietal, and occipital regions of the brain are shown in Figure 3.

**FIGURE 3 F3:**
[figure not shown]
Brain local regions.

### EEG analysis

The relative power of oscillations will be used to assess the effect of different frequencies of taVNS stimulation on the EEG of MCS patients (Bai et al., 2017). The relative power will be calculated as follows:

$$Relative\;Power\;(f_{1},f_{2})=Power\;(f_{1},f_{2})/Power\;(1,40)\;\times \;100\%,$$

where Power (*f*_1_,*f*_2_) indicates the absolute power between the low *f*_1_ and high *f*_2_ frequencies. Power (1,40) is the sum of power (1–40 Hz).

### taVNS and sham stimulations

The stimulation is provided by the SDZ-IIB electronic stimulator (Suzhou Medical Supplies Factory), which stably delivers continuous wave taVNS in the range of 1–100 Hz. In taVNS studies, the stimulation current intensity is commonly set according to the patient’s perception threshold, usually at 1–1.5 mA, depending on the patient’s tolerance (Badran et al., 2018). Based on previous experimental studies, we consider that the absence of a significant increase in heart rate, decrease in blood pressure, and painful expressions during stimulation mean that the patient tolerates the stimulation. Two silicone tips of the SDZ-IIB electronic stimulator are placed in the patient’s ear cavity and ear canal, and each patient receives five different frequencies of taVNS and a sham stimulus in a randomized order. The technical parameters of the sham stimulation are identical, but no current is passed through.

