### Procedures

The pilot study will begin as early as day 30 after the patient’s injury and will be completed within 1 year of the injury. Written informed consent will be obtained from the patient’s legal representative following an open discussion of the study objectives, methods, and potential risks. The patient’s legal representative will be informed that the patient’s legal representative has the right to ask the patient to withdraw from the study at any time during the course of the study and that each party will retain a copy of the signed informed consent form.

This is a prospective exploratory trial including 15 MCS patients, each receiving a total of five different frequencies of taVNS (1, 10, 25, 50, and 100 Hz) and a sham stimulus as a blank control for 20 min, where the order of stimulation is completely randomized. We chose these five frequencies to span the range used in previous taVNS studies, including our own. Patient’s CRS-R scores will be recorded before and after each stimulation. Each CRS-R score will be performed by no fewer than two physicians with extensive clinical experience. Also, by using a bedside 32-channel EEG (Nicolet EEG V32, Natus Neurology, USA), a 10-min resting EEG will be recorded before and after each stimulation, respectively. The interval between stimulations will be at least 48 h. SDZ-IIB electronic stimulator (Suzhou Medical Supplies Factory) will be used to provide stimulation. The experimental flow is shown in Figure 1.

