**FIGURE 1 F1:**
[figure not shown]
Single stimulation process and parameters used for stimulation.

Consistent with our previous experiments, a pair of identical-looking clips will be placed on both ears. The clips are designed with three carbon-impregnated silicone tips, one of which serves as the common end for supporting the posterior surface of the auricle, and the other two tips are designed to stimulate two skin surface points, one in the outer ear and the other in the navicular bone, with the two silicone tips at the outer ear point placed in the Cymba conchae and the Cavum conchae, respectively, as these are the two areas where the vagus nerve is most densely distributed in the ear. As shown in Figure 2, the SDZ-IIB electronic stimulator provides electrical pulses and continuous waves with a current of 1–1.5 mA. Real stimuli with frequencies of 1, 10, 25, 50, and 100 Hz are used on five occasions throughout the experiment, while a sham stimulus with the turned-off stimulator will be used on one occasion.

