## Discussion

Although previous studies have reported a positive effect of taVNS in the treatment of DOC patients, the efficacy is not stable due to different neuromodulation paradigms. Given the urgent therapeutic needs of DOC patients and the promising therapeutic prospects of taVNS, the scientific questions of optimal frequency parameters of taVNS should be urgently addressed.

The vagus nerve is the strongest parasympathetic nerve in the autonomic nervous system, consisting of 80% afferent and 20% efferent fibers, and serves as a bridge between the brain and the body in both directions (Butt et al., 2020). Vagus nerve stimulation is performed by electrically stimulating the vagus nerve to regulate brain activity (Shi et al., 2013). The distribution of the vagus nerve in the ear branch is mainly concentrated in the auricular region, including the Cymba conchae and the Cavum conchae (He et al., 2012). Therefore, electrical stimulation of the ear branch can produce similar effects to classical vagus nerve stimulation (Fang et al., 2016) without inducing perioperative risks.

The results of several previous studies have shown that taVNS modulates or activates cortical and subcortical areas associated with conscious control, including the locus coeruleus, nucleus accumbens, hypothalamus, medial prefrontal cortex, dorsolateral prefrontal cortex, anterior cingulate cortex, and posterior cingulate cortex (Kraus et al., 2007; Ruffoli et al., 2011; Cao et al., 2017; Corazzol et al., 2017).

In our previous study, we reported the effect of taVNS on cerebral hemodynamics in patients with DOC (Yu et al., 2021). Among 10 DOC patients included in the study, 5 responded to auditory stimulation and 5 showed no response. After 4 weeks of taVNS treatment, patients who responded to auditory stimulation had increased cerebral blood flow in several brain regions, a significant increase in CRS-R scores, and GOS scores indicating a good prognosis. In contrast, in patients who did not respond to auditory stimulation, the increase in cerebral blood flow with taVNS treatment was relatively weak, with a significant increase only in the left cerebellum and no significant changes in CRS-R scores or GOS scores. Therefore, our team suggests that the preservation of auditory function may be a key factor in response to taVNS in patients with DOC.

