In contrast to the previous study, we will eliminate the sparse wave treatment and replace it with a continuous wave treatment. This is because the experiment needs to control for a single variable frequency. Based on previous reports in the literature, we will use 1 Hz, 10 Hz, 25 Hz, 100 Hz, and sham stimuli as controls and 50 Hz as a supplement considering the large gap between the 25 and 100 Hz ranges. According to the existing literature (Sun et al., 2021), the retention effect of taVNS on the EEG lasts for about 1 h. Therefore, we will set a 48-h interval, i.e., a 48-h interval before the two stimuli, to ensure that the next stimulus does not receive the effects of the previous one.

In this study, we propose investigating the changes in behavior and brain function induced by taVNS in DOC patients using CRS-R and EEG measurements. In addition, the relative power of the oscillations will be used to assess the effects of different frequencies of taVNS on the EEG of MCS patients. Based on this, we will attempt to initially explore the selection of the optimal stimulation frequency parameters of taVNS for DOC patients through this experiment and to lay the foundation for subsequent experimental studies.

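### The tolerance rule counts a heart-rate rise but not a fall, so an isolated significant fall in heart rate is classed as tolerated

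*Protocol article*

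**What the plan says.** Three statements in the protocol article bear on this point.

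- **Current.** Methods, Procedures (the text on clip placement after Figure 1) says the stimulator delivers "electrical pulses and continuous waves with a current of 1–1.5 mA". The section on taVNS and sham stimulations describes intensity in taVNS studies as "usually at 1–1.5 mA, depending on the patient’s tolerance".
- **Tolerance.** The same section then gives the working definition, which it attributes to previous experimental studies: "the absence of a significant increase in heart rate, decrease in blood pressure, and painful expressions during stimulation mean that the patient tolerates" the stimulation. Three signs are listed, two of them with a direction: heart rate up, blood pressure down, pain visible.
- **Exposure.** Methods, Procedures has 15 patients, "each receiving a total of five different frequencies of taVNS", plus one sham session without current.

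The Discussion describes the target: "The vagus nerve is the strongest parasympathetic nerve in the autonomic nervous system, consisting of 80% afferent and 20% efferent fibers". It adds that stimulating the ear branch can act much as classical vagus nerve stimulation does. No other section mentions heart rate.

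**The concern.** The rule tells bedside staff when the current is acceptable. It covers a rise in heart rate and is silent on a fall, so a fall on its own passes.

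The omission is not neutral, for two reasons that come from the article itself. First, the rule already reaches beyond pain into the circulation, because it counts a drop in blood pressure. Counting that while passing a drop in heart rate makes the list inconsistent. Second, the article describes the stimulated nerve as parasympathetic with efferent fibres, and nothing in it explains why only a rise should matter.

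What is at stake is patient safety on a small scale. These patients cannot be relied on to say that they feel unwell, so a sign that the rule omits has no patient report to back it up. The claim is limited to the written rule. It is not that slowing is expected, nor that safety monitoring is absent from the trial.

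**Working it through.** The article gives no figure to reproduce. The check is on the logic of the rule.

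**Inputs**

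- Tolerance rule and its three signs: Methods, taVNS and sham stimulations.
- Current range 1–1.5 mA: Methods, Procedures.
- 15 patients and five active frequencies: Methods, Procedures.

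**Rule as written**

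Tolerated = no significant heart-rate rise AND no blood-pressure fall AND no painful expression.

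**All combinations**

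Heart rate has three states (rise, no significant change, fall), blood-pressure fall has two and painful expression has two: 3 × 2 × 2 = 12.

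| Heart rate | No BP fall, no pain | BP fall only | Pain only | BP fall and pain |
|---|---|---|---|---|
| Rise | not tolerated | not tolerated | not tolerated | not tolerated |
| No significant change | **tolerated** | not tolerated | not tolerated | not tolerated |
| Fall | **tolerated** | not tolerated | not tolerated | not tolerated |

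- Tolerated now: 2 of 12.
- Tolerated if a heart-rate change in either direction counts: 1 of 12 (no change, no fall in pressure, no pain).
- Reclassified: 2 − 1 = 1, the isolated heart-rate fall.
- Of the 4 combinations with a heart-rate fall, 3 are already not tolerated because pressure falls, pain shows, or both.

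These are counts of logical cases, not probabilities.

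**Exposure and largest effect on current**

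- Active sessions: 15 × 5 = 75.
- Largest reduction within the stated range: 1.5 − 1.0 = 0.5 mA, and 0.5 / 1.5 = 33%.

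The article gives no rate of isolated heart-rate falls, so the number of sessions affected cannot be estimated.

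**The case against.** The strongest reply is that leaving out one direction is a fault only if that direction is to be feared. The article draws no cardiac conclusion from its account of the nerve, and its Introduction calls the method safe in these patients. The rule is credited to earlier studies that are not available here, so its choice of signs cannot be checked against its source. It defines tolerance and is not presented as the trial's cardiac safety rule; a full protocol may hold separate monitoring. A fall in heart rate with a fall in pressure is already caught. Nor does the article say what staff do when stimulation is not tolerated, so a reduction in current is inferred. Finally, *significant* has no numeric limit, and the change leaves it so.

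Much of this stands, and it limits the size of the point. There is no event rate, the titration step is an inference, and other monitoring may exist. It does not remove the gap. The sentence is complete and operative, and as written it classes an isolated heart-rate fall as tolerated whatever another document may add. The general safety statement is also a weak reason to leave a direction out: the Discussion notes that most earlier studies in these patients used 20–25 Hz, whereas this trial also uses 1, 10, 50 and 100 Hz, with continuous-wave stimulation in place of the earlier waveform.

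**Conclusion.** The concern holds, as a minor safety correction. The written rule misplaces exactly one of 12 sign combinations, the isolated significant fall in heart rate, and it applies across 75 active sessions.

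This rests on reading the sentence as requiring all three signs to be absent, and on bedside signs being the main evidence of tolerance in patients who cannot reliably report. The 0.5 mA ceiling further assumes that intolerance leads to a lower current within 1–1.5 mA, which the article implies but does not spell out. How often an isolated fall would occur, and how harmful it would be, cannot be judged from the article.

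**What to change.** In Methods, taVNS and sham stimulations, replace the heart-rate condition with *a significant change in heart rate in either direction*. The blood-pressure and pain conditions stay as they are.

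The cost is one phrase. Heart rate must already be observed to apply the present rule, so nothing new is measured.

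The downside is that an occasional session may run at a lower current because of a benign fall, by at most 0.5 mA within the stated range. If current is set session by session, it could then differ between frequencies, whereas the Discussion says that "the experiment needs to control for a single variable frequency". The three existing signs already allow such differences; the change adds one more trigger. Recording the current delivered in each session would make any difference visible.

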### Behavioral assessments

The CRS-R is the recommended method for classifying the level of consciousness (American Congress of Rehabilitation Medicine Brain Injury-Interdisciplinary Special Interest Group Disorders of Consciousness Task Force et al., 2010). The patient’s level of consciousness is assessed using the CRS-R. This scale is the most valid and sensitive method for identifying behavioral signs of consciousness, leading to a better diagnosis of UWS/VS and MCS. It consists of six following subscales: auditory, visual, motor, oral-motor and verbal functions, communication, and arousal level. There are 23 items ordered by complexity, ranging from reflexive to cognitively mediated behaviors (Giacino et al., 2004).

### Data collection and management

All information collected in this study will be kept confidential. All data will be stored using encryption measures, and paper copies will be stored electronically and encrypted. Subjects’ legal representatives will be informed of the nature of the collected data and their rights to that same data through specific information sheets.

### Statistical analysis

SAS 9.4 (SAS Institute, Cary, Cary, NC, USA) statistical software will be used, and data analysis will be completed by a third-party (Clinical Evaluation Center of the Chinese Academy of Traditional Chinese Medicine) statistician. Filling of missing values: multiple filling methods will be used. The regression filling method will be used for monotonic missing data of measures, and Monte Carlo filling method will be used for arbitrary missing data; the logistic regression filling method will be used for monotonic missing data of counts, and the FCS filling method will be used for arbitrary missing data; the regression analysis will be used for sensitivity analysis.

## Discussion

Although previous studies have reported a positive effect of taVNS in the treatment of DOC patients, the efficacy is not stable due to different neuromodulation paradigms. Given the urgent therapeutic needs of DOC patients and the promising therapeutic prospects of taVNS, the scientific questions of optimal frequency parameters of taVNS should be urgently addressed.

The vagus nerve is the strongest parasympathetic nerve in the autonomic nervous system, consisting of 80% afferent and 20% efferent fibers, and serves as a bridge between the brain and the body in both directions (Butt et al., 2020). Vagus nerve stimulation is performed by electrically stimulating the vagus nerve to regulate brain activity (Shi et al., 2013). The distribution of the vagus nerve in the ear branch is mainly concentrated in the auricular region, including the Cymba conchae and the Cavum conchae (He et al., 2012). Therefore, electrical stimulation of the ear branch can produce similar effects to classical vagus nerve stimulation (Fang et al., 2016) without inducing perioperative risks.

The results of several previous studies have shown that taVNS modulates or activates cortical and subcortical areas associated with conscious control, including the locus coeruleus, nucleus accumbens, hypothalamus, medial prefrontal cortex, dorsolateral prefrontal cortex, anterior cingulate cortex, and posterior cingulate cortex (Kraus et al., 2007; Ruffoli et al., 2011; Cao et al., 2017; Corazzol et al., 2017).

In our previous study, we reported the effect of taVNS on cerebral hemodynamics in patients with DOC (Yu et al., 2021). Among 10 DOC patients included in the study, 5 responded to auditory stimulation and 5 showed no response. After 4 weeks of taVNS treatment, patients who responded to auditory stimulation had increased cerebral blood flow in several brain regions, a significant increase in CRS-R scores, and GOS scores indicating a good prognosis. In contrast, in patients who did not respond to auditory stimulation, the increase in cerebral blood flow with taVNS treatment was relatively weak, with a significant increase only in the left cerebellum and no significant changes in CRS-R scores or GOS scores. Therefore, our team suggests that the preservation of auditory function may be a key factor in response to taVNS in patients with DOC.

Our recent study focused on the EEG changes in 12 DOC patients before and after 14 days of taVNS treatment (Yifei et al., 2022), revealing a decrease in δ-band energy and an increase in β-band energy in the EEG of MCS patients after treatment, while no significant changes were observed in VS. Therefore, in this experiment, we used the diagnosis of MCS and preservation of auditory function as important screening criteria in order to improve the success rate.

By reviewing six studies on tavNS for patients with DOC, Jang and Cho (2022) found that four studies reported positive outcomes in patients with DOC treated with taVNS, including two EEG studies and two fMRI studies. However, in terms of stimulation frequency, 20–25 Hz was chosen by most studies, probably because there were no studies on the optimal stimulation frequency of taVNS in patients with DOC. Accordingly, the FDA-approved frequency range of 20–30 Hz for vagus nerve stimulation ensued.

The range of stimulation frequencies along the vagus nerve is clearly lacking in consideration for taVNS. We found that different stimulation frequencies may be appropriate for taVNS in different diseases. Also, different frequencies for the same disease produce different therapeutic effects. E.g., Marsal et al. (2021) innovatively boosted the taVNS stimulator to 2 kHz for the treatment of rheumatoid arthritis disease, and after 12 weeks of treatment, the mean DAS28-CRP significantly decreased in 27 patients compared to baseline, demonstrating that a 100-fold higher treatment frequency was more effective in patients with rheumatoid arthritis than the conventional 20 Hz. In another study, 24 patients with migraine were randomized into two groups, one of which was treated with 1 Hz, and the control group was treated with 20 Hz, both for 4 weeks. The results showed that after 4 weeks of treatment, the efficacy of 1 Hz was significantly due to 20 Hz (Cao et al., 2021).

In contrast to the previous study, we will eliminate the sparse wave treatment and replace it with a continuous wave treatment. This is because the experiment needs to control for a single variable frequency. Based on previous reports in the literature, we will use 1 Hz, 10 Hz, 25 Hz, 100 Hz, and sham stimuli as controls and 50 Hz as a supplement considering the large gap between the 25 and 100 Hz ranges. According to the existing literature (Sun et al., 2021), the retention effect of taVNS on the EEG lasts for about 1 h. Therefore, we will set a 48-h interval, i.e., a 48-h interval before the two stimuli, to ensure that the next stimulus does not receive the effects of the previous one.

In this study, we propose investigating the changes in behavior and brain function induced by taVNS in DOC patients using CRS-R and EEG measurements. In addition, the relative power of the oscillations will be used to assess the effects of different frequencies of taVNS on the EEG of MCS patients. Based on this, we will attempt to initially explore the selection of the optimal stimulation frequency parameters of taVNS for DOC patients through this experiment and to lay the foundation for subsequent experimental studies.

## Data availability statement

The original contributions presented in this study are included in the article/supplementary material, further inquiries can be directed to the corresponding authors.
